### Procedure

Patients will be recruited during consultations in the Rheumatology and Spine surgery units of all participating hospitals. Patients who fulfil the inclusion criteria will be informed about the goals and execution of the study and written informed consent will be obtained. Baseline and follow-up data will be collected by physicians assisted by study nurses. An overview of the study flow is given in Figure 1. In a preliminary phase of the study we will validate the German version of the Swiss Spinal Stenosis Questionnaire. This questionnaire is recommended for outcome measurement by the North American Spine Society.

**Figure 1 F1:**
[figure not shown]
**Study flow**.

After quality control all data will be stored in a central data base. All the recorded data and information contained within the study will remain strictly confidential. All the personal data will be made anonymous and assigned a code. The decoding will be stored at the Horten Centre and will be accessible only to the principle investigator. We will ensure that anonymization is maintained throughout any collaboration with other investigators. The data management will comply with the federal law of data protection of Switzerland.

### Treatment

The choice of treatment is not influenced by participation in the study and depends only on the clinical situation, physician's advice, and patients decision. Treatment options are watchful waiting, conservative treatment with physical therapy and/or drugs, epidural injections of analgesics and/or steroids and surgery. Detailed information about treatment(s) will be recorded using pre-specified questionnaires at each follow up visit. The questionnaire will comprise specific questions about: mode, duration and frequency of physical therapy; duration and dosage of drug treatments; site of epidural injection, with or without imaging, dosage of injected drugs; surgeon, precise and detailed description of surgical technique and procedure, intra- and postoperative complications, duration of surgical procedure and duration of hospital stay. Only experienced surgeons who have performed more than one hundred operations on the lumbar spine within the last two years will be included in the study.

### Data to be collected

At baseline information about socio-demographic characteristics, symptoms, clinical examination, consumption of analgesics and other treatments for lumbar spinal stenosis within the last 6 months will be collected. Radiological findings (CT, MRI) at different measurement points between lumbar vertebra 1 to lumbar vertebra 5 (central stenosis: antero-posterior diameter of spinal canal, cross sectional area of dural tube, interpedicular distance[29-31]; lateral stenosis: height and depth of the lateral recess [32-35]; foraminal stenosis: foraminal diameter will be quantified [36].

Comorbidities will be assessed with the validated Cumulative illness rating scale (CIRS) [37] which rates the presence and severity of comorbid diseases in 13 organ systems from 0 to 4, and sums organ-specific scores across systems to yield a summary score. Depression, a prognostic indicator, will be quantified with the Hospital Anxiety and Depression Score (HADS). The questionnaire consists of 14 questions, seven for anxiety and seven for depression [38].

Information about treatment will be collected at baseline for six months preceding enrolment in the study and at each follow-up visit for the period between the visits.

### Outcome measures (baseline and follow up)

Primary and secondary outcome data will be collected at baseline and at six weeks and six months after the time of treatment onset (surgery for the surgery group and time of enrolment for the nonsurgical group). Long-term outcome data will be gathered after one year and then annually up to three years.

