**Methods/Design:**

This is a prospective, multi-centre cohort study within four hospitals of Zurich, Switzerland. We will enroll patients with neurogenic claudication and lumbar spinal stenosis verified by Computer Tomography or Magnetic Resonance Imaging. Participating in the study will have no influence on treatment modality. Clinical data, including relevant prognostic data, will be collected at baseline and the Swiss Spinal Stenosis Questionnaire will be used to quantify severity of symptoms, physical function characteristics, and patient's satisfaction after treatment (primary outcome). Data on outcome will be collected 6 weeks, and 6, 12, 24 and 36 months after inclusion in the study. Applying multivariable statistical methods, a prediction rule to estimate the course after surgery will be derived.

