### Objectives

1. To develop a prognostic probability function (prediction rule) in order to predict the further course (one, two and three years after diagnosis) *in patients with lumbar spinal stenosis undergoing surgery.*

2. To develop (a) prognostic probability function(s) (prediction rules) in order to predict the further course (one, two and three years after diagnosis) in *patients with lumbar spinal stenosis treated, at least initially, by conservative measures.*

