### Study sample size

Sample size is calculated for objective one, the development of a prognostic function for patients undergoing spine surgery, one year after surgery. Outcome after surgery will be quantified by the Swiss Spinal Stenosis Questionnaire (SSM)[28] and results will be dichotomized. An improvement of more than 0.5 points on the symptom severity scale and physical function scale in the SSM will be categorized as improved. According to the original publication [28] 0.5 points represents a clinically relevant improvement for the patients (Minimal Clinical Important Difference). We estimate that 60% of all patients with verified diagnosis will undergo surgery and two thirds of these (between 60% and 70%) of patients will show an improvement of more than 0.5 points in both scales (symptom severity and physical function) one year after surgery. To estimate the effect of ten prognostic variables we need roughly 100 patients without improvement, as defined above, after surgery. This leads us to include 350 patients in the study who undergo surgery.

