### Primary Outcome

The Swiss Spinal Stenosis Questionnaire (SSM)[28] has been recommended by the North American Spine Society (NASS) [1] as the "gold standard" to quantify outcome in patients with spinal stenosis, will be used to quantify outcome. The SSM consists of three different subscales; severity of symptoms (possible range of the score is 1 to 5), physical function characteristics (possible range of scores is 1 to 4) and patient's satisfaction after treatment (the range of the scale is 1 to 4). In the present study, both the severity of symptoms and the physical function scales will represent the primary outcome, whereby a minimum of 0.5-point change in each will be required for the treatment to be considered a success. The SSM has been used as the primary outcome in different studies on lumbar spinal stenosis [39-43] and a German version is available.

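### For operated patients the protocol starts the outcome clock at three different dates (inclusion, diagnosis and surgery), and the visit the study is sized on names none of them

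*Protocol article*

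**What the plan says.** Four places in the article date the outcome.

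- Abstract, Methods/Design: "Data on outcome will be collected 6 weeks, and 6, 12, 24 and 36 months after inclusion in the study". This applies to all patients, operated or not.
- Objectives: both rules, including the one for surgical patients, are to "predict the further course (one, two and three years after diagnosis".
- Study sample size: the calculation is for "the development of a prognostic function for patients undergoing spine surgery, one year after surgery".
- Outcome measures (baseline and follow up): data are taken at baseline and "six weeks and six months after the time of treatment onset (surgery for the surgery group and time of enrolment for the nonsurgical group". The following sentence reads "Long-term outcome data will be gathered after one year and then annually up to three years" and gives no starting point.

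Two further statements bear on the reference value. Under Data to be collected, "Information about treatment will be collected at baseline for six months preceding enrolment in the study", which ties baseline to enrolment. Under Primary Outcome, "a minimum of 0.5-point change in each will be required for the treatment to be considered a success"; the text does not say from which measurement the change is counted.

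The second objective concerns patients "treated, at least initially, by conservative measures". Surgery some time after enrolment is therefore foreseen.

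**The concern.** The endpoint of Objective 1 is a dichotomised change score at a fixed horizon. It is defined only once both ends of the interval are fixed, and the article gives competing answers for one end and leaves the other implicit.

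If sites schedule from inclusion, operated patients with different waits contribute different lengths of recovery to one nominal one-year result, and some early postoperative visits take place before the operation. If the analysis follows the objectives and counts from diagnosis, the rule predicts something other than the one-year postoperative result for which the study was sized. Statistical analysis also allows Cox models, which need one time zero.

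Where the operation follows a period of conservative care, a change counted from enrolment combines what happened before surgery with what happened after it. The prognostic values used in the rule would also date from before that period.

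**Working it through.** **Step 1. How many distinct origins?** The outcome section defines treatment onset as surgery for the operated group and enrolment for the others. Treatment onset is therefore not an origin of its own.

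| Place | Clock for operated patients | Clock for non-operated patients |
|---|---|---|
| Abstract | inclusion | inclusion |
| Objectives | diagnosis | diagnosis |
| Study sample size | surgery | not applicable |
| Outcome section, six weeks and six months | surgery | enrolment |
| Outcome section, one to three years | not named | not named |

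Operated patients have three origins: inclusion, diagnosis and surgery. For non-operated patients the abstract and the outcome section agree if inclusion and enrolment are the same date; only the objectives differ.

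**Step 2. Can the dates differ?** Eligibility requires a verified diagnosis but states no limit on its age, so diagnosis can precede inclusion. Recruitment covers rheumatology as well as surgical units (Procedure), treatment choice is left open (Treatment), and Objective 2 expects initial conservative care. Surgery can therefore follow inclusion by some interval. The article gives no figure for it.

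**Step 3. Size on the inclusion clock.** Let w be the months from inclusion to surgery (an assumption). Postoperative time at a visit = scheduled time after inclusion − w. Six weeks is 6 × 12/52 ≈ 1.4 months.

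| w (months) | 6-week visit | 6-month visit | 12-month visit | 24-month visit | 36-month visit |
|---|---|---|---|---|---|
| 0 | 1.4 | 6 | 12 | 24 | 36 |
| 1 | 0.4 | 5 | 11 | 23 | 35 |
| 2 | −0.6 | 4 | 10 | 22 | 34 |
| 3 | −1.6 | 3 | 9 | 21 | 33 |
| 6 | −4.6 | 0 | 6 | 18 | 30 |

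Entries are months after surgery; a negative entry means the visit is preoperative. The six-week visit becomes preoperative once w exceeds about 1.4. On the diagnosis clock, replace w by the interval from diagnosis to surgery.

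**Step 4. Size on the surgery clock.** The one-year visit is 12 months after surgery for everyone, so the timing problem disappears. The reference value remains. Count improvement as positive. Then

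recorded change = (change from enrolment to just before surgery) + (change from just before surgery to one year after).

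A patient who worsens by δ points while waiting needs a postoperative gain of 0.5 + δ to reach the 0.5-point threshold. One who improves by δ needs only 0.5 − δ. The article gives no data on δ.

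**Step 5. The plan's own figure.** The schedule carries no calculated figure. The target of 350 operated patients does not enter the argument: with 60% to 70% improved, it yields 350 × 0.40 = 140 to 350 × 0.30 = 105 without improvement, which meets the stated need of roughly 100. That count is defined one year after surgery, the horizon that the outcome section leaves without an origin.

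**The case against.** The best defence is that the operative Methods text already points to surgery. The sample size section says so, and the outcome section anchors the operated group there. The long-term sentence follows directly and is naturally read on the same clock. On that reading the abstract's line is only a loose summary. This stands in part: nobody may conclude that one-year results will in fact be taken at varying postoperative times. A reader might infer that, but it holds only if the inclusion or diagnosis clock is the one followed. The defence does not cover the objectives, which belong to the same Methods section and set the surgical rule's horizon from diagnosis.

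It is also fair that this is a condensed article, that the study-flow figure is not shown, and that visit windows and repeat-visit rules often sit in the full protocol. So the lack of a described preoperative repeat is not by itself an error. The contradictory clocks are statements in the text, not omissions.

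A reader might also call the baseline undefined. It is not, because the text ties it to enrolment. What is unstated is which value serves as the reference when surgery comes later.

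**Conclusion.** The point holds in this form: three incompatible time origins are stated for operated patients, and the one- to three-year visits have none. The conflict affects when the primary outcome is measured and what the Objective 1 rule predicts. It should be fixed. It does not show that the data will be unusable, because part of the Methods already points to surgery as time zero.

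The conflict itself rests on no assumption. Its size does: the shift equals the wait w, for which the article gives no value, so the table above is illustrative. The reference-value problem is confined to patients operated on some time after enrolment.

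Two stronger inferences are tempting and unsupported. One is to take the 43% two-year crossover quoted in the background from a randomised trial and derive how many of the 350 operations would be delayed. That figure describes patients allocated to conservative care, whereas here patient and physician choose, so it does not carry over. The other is that the timing error would be systematic because waiting time follows severity or hospital. This is plausible, but nothing in the document says it.

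**What to change.** Use one time zero per objective and make the four places agree.

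- Objective 1: date of surgery, with horizons 12, 24 and 36 months after surgery.
- Objective 2: date of enrolment, with horizons at one, two and three years from it.
- Abstract: replace the reference to inclusion by the group-specific origin.
- Objectives: replace the reference to diagnosis by the origin of each objective.
- Outcome section: name the origin of the one- to three-year visits.
- Primary Outcome: define the Objective 1 change from the last questionnaire and predictor values before surgery. State how a patient first treated conservatively and operated on later is re-anchored.

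The cost is wording and visit-window programming. Repeating the questionnaires shortly before a delayed operation would give a cleaner reference value for a small extra data-collection burden. It is optional, and reconciling the text does not depend on it.

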### Primary Outcome

The Swiss Spinal Stenosis Questionnaire (SSM)[28] has been recommended by the North American Spine Society (NASS) [1] as the "gold standard" to quantify outcome in patients with spinal stenosis, will be used to quantify outcome. The SSM consists of three different subscales; severity of symptoms (possible range of the score is 1 to 5), physical function characteristics (possible range of scores is 1 to 4) and patient's satisfaction after treatment (the range of the scale is 1 to 4). In the present study, both the severity of symptoms and the physical function scales will represent the primary outcome, whereby a minimum of 0.5-point change in each will be required for the treatment to be considered a success. The SSM has been used as the primary outcome in different studies on lumbar spinal stenosis [39-43] and a German version is available.

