### Statistical analysis

Epidemiologic data and patients' descriptive data available on continuous scales will be presented with medians, interquartile ranges or means and standard deviations as appropriate. Categorical data will be presented as rates and percentages. Associations of the continuous independent variables with the outcome variables will be reported using simple logistic regressions. Results from univariate analysis will guide multivariable modeling.

Assessment of associations will be performed using multi-variable models including potential confounders along with the independent variables of interest. Prognostic scores will be built using either logistic regression analysis or Cox proportional hazard models. Models will be validated in subsamples by cross validation. Calibration and discrimination of the cross-validated prognostic instruments will be assessed using the Brier Score.

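### Patients who start within 0.5 points of the best score on either SSM scale are counted as failures by construction, and nothing keeps the baseline scores in the prognostic model

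*Protocol article*

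**What the plan says.** The protocol article fixes the primary outcome in two places.

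- **Primary Outcome** gives the ranges as "severity of symptoms (possible range of the score is 1 to 5), physical function characteristics (possible range of scores is 1 to 4"), and states that "a minimum of 0.5-point change in each will be required for the treatment to be considered a success".
- **Study sample size** states that "results will be dichotomized" and that "An improvement of more than 0.5 points on the symptom severity scale and physical function scale in the SSM will be categorized as improved". It justifies the threshold by citing the original publication: "0.5 points represents a clinically relevant improvement for the patients (Minimal Clinical Important Difference").

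Three other sections bear on the point.

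- **Eligibility Criteria and identifying patients** requires neurogenic claudication and imaging-verified stenosis. None of its six inclusion or four exclusion criteria refers to an SSM score.
- **Outcome measures (baseline and follow up)** has the primary outcome data collected at baseline, so both baseline scores will be available.
- **Statistical analysis** plans simple logistic regressions for the continuous variables and adds: "Results from univariate analysis will guide multivariable modeling". It also says that the multivariable models will include potential confounders. It does not name baseline SSM as a term that is always in the model.

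**The concern.** A patient cannot gain more than the distance from the starting score to the best score. Where that distance is too short on either scale, the outcome is settled at enrolment and neither treatment nor prognosis can alter it. Because both scales must improve, one near-normal scale is enough.

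This matters because the product is a prediction rule meant to help patients and physicians choose a therapy. The Treatment modalities section reports that poorer self-rated preoperative health and limited walking ability predict an unfavourable result. If that holds here, severe patients fail more often for prognostic reasons while near-floor patients fail by definition, so the relation between baseline score and improvement may rise and then fall. A simple logistic regression with one linear term could show little association even though baseline matters at both ends. If baseline were then dropped, predictors that go along with a low baseline score would absorb part of the artefact and look unfavourable for a reason that is not prognostic.

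**Working it through.** **The plan's own figure.** The sample size rests on roughly 100 non-improvers for ten variables, with 60% to 70% improving. The number of surgical patients needed is 100 / (1 − improvement rate):

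- 60%: 100 / 0.40 = 250
- two thirds: 100 / 0.333 = 300
- 70%: 100 / 0.30 = 333.3, rounded up to 334

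The planned 350 exceeds all three. It yields 350 × 0.40 = 140, 350 / 3 = 117 or 350 × 0.30 = 105 non-improvers, so it is a conservative rounding.

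**Who cannot succeed.** The direction of the two scales is not stated; I take 1 as best. The largest possible gain is then baseline − 1.

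- Primary Outcome wording (gain of 0.5 suffices): success needs baseline − 1 ≥ 0.5, so anyone below 1.5 on either scale fails.
- Study sample size wording (gain must exceed 0.5): success needs baseline − 1 > 0.5, so anyone at or below 1.5 on either scale fails.

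A patient at exactly 1.5 who reaches the best score is a success under one section and a failure under the other. The first section also speaks of a change, the second of an improvement.

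**How many.** The article gives no baseline mean or SD, so this step is assumption throughout. For the function scale, with an assumed normal distribution, the share at or below 1.5 is Φ((1.5 − mean) / SD). The last column divides by the 117 non-improvers expected at two thirds.

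| Assumed mean, SD | z | Share | Of 350 | Relative to 117 |
|---|---|---|---|---|
| 2.6, 0.5 | −2.20 | 1.4% | 5 | 4% |
| 2.4, 0.6 | −1.50 | 6.7% | 23 | 20% |
| 2.2, 0.7 | −1.00 | 15.9% | 56 | 48% |

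A second set of assumptions took both scales together: symptom mean 2.8 to 3.0, function mean 2.0 to 2.5, SD 0.5 to 0.7, correlation 0.5. It puts about 2% to 25% below 1.5 on at least one scale. The symptom scale alone accounts for only 0.1% to 3.1%, so under these inputs the function scale drives the result.

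**The case against.** The strongest reply has four parts.

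- **The patients may be few.** Eligibility requires claudication, and the sample size concerns patients who go on to surgery. A near-best symptom score is unlikely among them. This stands, and it is why the point is confined to patients within 0.5 of the best score. A reader might infer that mild patients in general are automatic failures; the arithmetic does not support that. The function scale remains open, as does the conservatively treated cohort of the second objective, where low scores may be more common.
- **Room to improve is legitimate predictive information.** A patient with little to gain does have a low chance of a 0.5-point gain. This also stands, but only if baseline is in the model, so that the artefact is carried there and not by other variables.
- **The analysis section does not exclude baseline.** It says that univariate results guide the modelling, not that they alone decide, and it allows for confounders. To say that baseline enters only if the screen favours it would go beyond the text. What stands is that the screen is given a guiding role and is poorly suited to a relation that may not be monotone.
- **Dichotomising is deliberate.** A reader might go further and hold that cutting the score wastes about 40% of the information, so that a continuous model should replace it. For one normal variable split at two thirds, the large-sample loss is indeed 40.5% (38% to 42% over 60% to 70%). The documents do not support treating this as a defect. The Abstract sets the probability of clinically relevant improvement as the target, the threshold is a cited minimal important difference, and the study is already sized on the binary outcome. Separate continuous models for the two scales would also not give the probability of gaining on both; that needs a joint model.

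**Conclusion.** The point holds in a limited form. The success definition makes improvement impossible for patients within 0.5 points of the best score on either scale, and the article neither says how they are handled nor secures the baseline scores in the model. The only assumption in that statement is that 1 is the best score.

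The size is unknown. The range of about 1% to 16% rests entirely on assumed function means and SDs and on a normal shape for a bounded scale; no value within it can be preferred from the article. Distortion of other predictors is a risk and not a certainty: it needs baseline to be left out or modelled too simply. The point does not show that 350 is too small or that the binary target is wrong. It is worth correcting because the remedy is cheap and the data are already to be collected.

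**What to change.** 1. In Statistical analysis, state that both baseline SSM scores enter every prognostic model as continuous terms, with non-linearity allowed, whatever the univariate results show.
2. Report, for the surgical and the conservatively treated patients, how many cannot reach success because of their baseline score. Add a sensitivity analysis that excludes them.
3. Reconcile the threshold between Primary Outcome and Study sample size: whether a gain of exactly 0.5 counts, and that the change must be an improvement.
4. Keep the dichotomised outcome as the main target. A model of the continuous scores is at most an optional secondary analysis.

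The cost is mainly wording. The baseline terms take at least two of the ten predictor slots. If each non-linear term adds one parameter on top of ten variables, the model has 12, and the expected 105 to 140 non-improvers give 105 / 12 = 8.8 to 140 / 12 = 11.7 per parameter, against 10.5 to 14.0 for ten. The alternative is to carry fewer other candidates. The sensitivity analysis also loses events: in the assumed 6.7% case at two thirds improvement, 117 − 23 = 94 non-improvers would remain among 350 − 23 = 327 patients.
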